**Fig. 1 Fig1:**
[figure not shown]
Separate the ovarian vessels and protect the ureter

**Fig. 2 Fig2:**
[figure not shown]
Sever the ovarian vessels

**Fig. 3 Fig3:**
[figure not shown]
Dislocate the fat flap with 10–15 cm in total length

**Fig. 4 Fig4:**
[figure not shown]
The fat flap containing ovarian vascular pedicle packed between the anastomotic stoma and vagina, then fixed with medical fibrin glue

#### Group B (control group)

All operations will be performed according to the principle of TME radical resection in rectal cancer surgery.

### Criteria for discontinuing or modifying allocated interventions {11b}

The patient has complications before surgery.The patient agrees to the study but refuses to be randomly assigned.Conditions not suitable for the protocol are found during surgery. For example, during the surgical process, it is found that the patient does not have a suitable free fat flap with ovarian vascular pedicle available, or there is a need to change the surgical method or expand the surgical scope in crisis situations such as bleeding during the operation, or special circumstances with the location, size, and surrounding tissues discovered during the operation.The patient asks to be withdrawn from the protocol.The patient would be unable to continue the protocol due to other postoperative complications.Patients lost to follow-up.

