### Objectives {7}

In this study, packing the anastomotic stoma with a laparoscopic dislocated fat flap containing ovarian vascular pedicle anterior to the anastomosis to explore whether a statistically significant difference in the incidence of rectovaginal leakage between the experimental group and the control group. Thus, we study the feasibility of this method for the prevention of postoperative rectovaginal fistula, and to provide effective clinical evidence for the prevention of postoperative RVF. The purpose study’s main aim is to evaluate the intervention’s efficacy while analyzing feasibility. The purpose of the study is to evaluate the effectiveness of the intervention methods (preventing rectovaginal fistula) in the experimental group, as well as the feasibility of their clinical implementation and promotion. Finally, we attempt to analyze the population suitable for using this method from the final statistical data.

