### Intervention description {11a}

#### Group A (experimental group)

All operations will be performed according to the principle of TME radical resection in rectal cancer surgery. The anterior rectal wall of about 1 cm distal to the anastomosis will be dislocated.Before the rectal anastomosis, the researcher would expose one side of the ureter (usually the left side), dislocate the fat flap containing ovarian vascular pedicle to avoid damage of the ureter, and dissect ovarian vessels proximal to the kidney. After dislocating the fat flap, the size of the packing end would be 2 cm (width) × 4–5 cm (length) at least, with a 10–15 cm in total length, which would be measured by a thread during the operation. This length would ensure to pull-down to 5 cm below the anastomosis (Figs. 1, 2, and 3).After rectal anastomosis, a large amount of normal saline will be used to rinse the pelvic cavity. The liquid will be sucked up. The surface of the rectum and vagina will be dried with gauze.The fat flap containing ovarian vascular pedicle will be flipped downward and packed between the anastomotic stoma and vagina (9 o’clock to 3 o’clock of the outer wall of the rectum in lithotomy position), then fixed with medical fibrin glue. (Fig. 4)

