### Relevant concomitant care permitted or prohibited during the trial {11d}

The similar type of surgery is prohibited during the trialOther complications arising from the procedure can be managed during the trial.Patients who drop out of the experiment during the course of the study will be no longer included in the analyses.Patients with other fatal complications will be no longer included in the analyses.All routine treatment procedures for women in care for low and medium rectal cancer, as deemed appropriate by the patient’s treating clinicians, will be permitted during the trial.Additional clinical review, further treatments, including treatment of rectovaginal fistula, and concomitant medications will be determined by clinical need and will be recorded in follow-up case report forms.

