### Sample size {14}

Female patients with low and medium rectal cancer in the Department of Colorectal Surgery, Fujian Medical University Union Hospital, from April 2020 to March 2023 are selected as the research participants. It is assumed that the RVF of the study group is the same as that of the control group. According to previous research results and relevant literature reports, the incidence of RVF of the control group and the test group was set at 9.9%, the non-inferior margin value was set at 15%, the test level was set at 0.05, and the power was set at 0.8 [1, 2]. The sample size was calculated by SPSS24.0 software as follows: *N* = 115, and each group needed 115 people. We assume that 20% of patients would be lost to follow-up, and 144 would need to be enrolled.

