## Statistical methods

### Statistical methods for primary and secondary outcomes {20a}

The independent statistician is responsible for the statistical analysis with SPSS 24.0 software. Patient data that falls off will not be included in the analysis. In the statistical analysis, measurement data between the two groups will be analyzed with the *t*-test and rank-sum test, while categorical data will be analyzed with *χ*^2^ test. Data will be recorded as mean ± standard deviation or median (first quartile, third quartile). The experiment is a non-inferiority trial, and the statistical method is mainly based on “parameter estimation.” Using the primary endpoint, determine the confidence interval for the difference in the efficacy of surgical methods in preventing rectovaginal fistula between the control group and the cases group. The significance level used for statistical analysis will be two-sided with confidence intervals at the 95% level.

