### Methods in analysis to handle protocol non-adherence and any statistical methods to handle missing data {20c}

We perform statistical analysis on the complete case. The complete case is that all the data required for this study protocol are complete and there are no missing cases in order to be included in the final statistical analysis. The premise of this RCT is that it does not violate the treatment principles of the patient's disease and does not imply or modify the patient's treatment intention. The experiment respects the treatment willingness of each enrolled patient.

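### The rule on patients found at surgery to have no usable flap, read with the dropout and complete-case rules, may remove patients from Group A only

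*Protocol article*

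**What the plan says.** All of this is in the protocol article.

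- **Criteria for discontinuing or modifying allocated interventions {11b}.** One criterion is that "Conditions not suitable for the protocol are found during surgery". The first example given is that "during the surgical process, it is found that the patient does not have a suitable free fat flap with ovarian vascular pedicle available". The same list also holds patients who ask to withdraw and patients lost to follow-up.
- **Relevant concomitant care {11d}.** "Patients who drop out of the experiment during the course of the study will be no longer included in the analyses".
- **Statistical methods {20a}.** "Patient data that falls off will not be included in the analysis". The trial is described there as a non-inferiority trial judged on a 95% confidence interval.
- **Non-adherence and missing data {20c}.** The analysis is on complete cases, defined thus: "The complete case is that all the data required for this study protocol are complete and there are no missing cases".
- **Group A and Group B.** Only Group A has the flap dissected. Its length is checked intraoperatively, "which would be measured by a thread during the operation". Group B has the TME resection alone.
- **Objectives {7}.** The aim covers efficacy "as well as the feasibility of their clinical implementation and promotion". The authors also hope to identify, from the final data, which patients suit the method.
- **Sample size {14}.** "We assume that 20% of patients would be lost to follow-up, and 144 would need to be enrolled". The allowance names loss to follow-up and nothing else.

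**The concern.** Randomisation makes the two groups alike in anatomy, including the share of women whose ovarian pedicle would not yield a usable flap. In Group A the surgeon finds out who they are. In Group B nobody looks. If that finding takes a woman out of the analysis, Group A is analysed without its unsuitable anatomy and Group B with it, so the comparison is no longer between the groups that were randomised. If pedicle anatomy goes with fistula risk, the difference is biased.

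Feasibility is also at stake. If women in whom the flap could not be raised leave the data, the flap has been placed in every Group A woman who remains, and the final data cannot show who was unsuitable.

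**Working it through.** **1. Does the event fall after randomisation, and in one arm?** Sequence generation {16a} places randomisation after recruitment, and Implementation {16c} has the envelope opened before the assigned operation. The flap is sought during that operation, in Group A only. The event is therefore post-randomisation and, in practice, confined to Group A. Other triggers in {11b}, such as bleeding or a change of surgical method, can arise in either arm.

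**2. Does the event lead out of the analysis?** {11b} does not say so. It sits in one list with withdrawal and loss to follow-up, which are dropouts; {11d} and {20a} exclude dropouts; and {20c}, whose heading covers protocol non-adherence, offers complete cases only. No section says that a woman without a flap stays in Group A. Exclusion is thus a natural reading, but an inferred one.

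**3. The plan's own figure.** 115 / (1 - 0.20) = 143.75, so 144: the dropout step reproduces. The 115 per group does not follow from 9.9% in both arms, a 15-point margin and 80% power. The usual formula, 2 x 0.099 x 0.901 x (z_alpha + z_beta)^2 / 0.15^2, gives 62.2 (63 per group) at one-sided 0.025 and 49.0 (50 per group) at one-sided 0.05. That is a separate matter, and nothing here depends on it.

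**4. Possible size, on assumptions.** The article gives neither the share of women without a usable flap (x) nor their fistula risk (q), so both are assumed. Suppose the flap has no effect and the true rate is 9.9% in both arms. After removal, the Group A rate is

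(9.9% - x q) / (1 - x).

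| x removed from A | q = 4.95% | q = 9.9% | q = 20% | q = 30% |
|---|---|---|---|---|
| 5% | 10.2% | 9.9% | 9.4% | 8.8% |
| 10% | 10.4% | 9.9% | 8.8% | 7.7% |
| 20% | 11.1% | 9.9% | 7.4% | 4.9% |

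For example, x = 20% and q = 30% gives (9.9 - 6.0) / 0.8 = 4.9%. The shift runs from +1.2 points (11.1 - 9.9) to -5.0 points (4.9 - 9.9), and is zero when q equals the average risk.

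**5. Would it decide non-inferiority?** Take the cell least favourable to Group A: x = 20%, q = 4.95%, rate 11.14%. With 115 analysed in B and 115 x 0.8 = 92 in A, the standard error is sqrt(0.1114 x 0.8886 / 92 + 0.099 x 0.901 / 115) = 0.043. The upper 95% limit is 1.24 + 1.96 x 4.3 = 9.7 points. The article does not make clear whether 144 is per group or in total. If it is the total, 72 per group less 20% leaves about 58 in B and 46 in A, and the same calculation gives 13.1 points. Both limits are below 15. In the opposite corner (x = 20%, q = 30%) the limit at 92 v 115 is 2.0 points, so removal would then make non-inferiority look easier than it is.

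**6. Feasibility.** With x = 10% of 144 randomised to Group A, about 14 leave. The flap is then complete in 130/130 (100%) of those analysed, against 130/144 (90%) of those randomised. The 10% is again an assumption.

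**The case against.** The strongest reply is that exclusion is never stated. {11b} governs the intervention, not the analysis set. A Group A woman who has her resection without a flap and attends every visit has not dropped out, and on a literal reading of {20c} she is a complete case. This stands: the fault is a set of rules that permits one-arm removal and contains nothing to prevent it. It is still more than detail left to an analysis plan, because the article itself fixes the exclusion and complete-case rules.

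Two further points stand. The outcomes section lists no technical-success outcome, so the protocol does not promise a success rate that would be inflated; and the retention section {18b} has staff monitor reasons for discontinuation, so flap failures could be counted. But {18b} does not put those women back into the analysis. The exclusion of women with prior hysterectomy, oophorectomy or major abdominal surgery may also make an unusable pedicle less common.

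A reader might try to bound the failure rate from the 39 earlier cases in the Discussion: no failures in 39 would give an exact upper 95% limit of 1 - 0.025^(1/39) = 9.0%. The documents do not support this. Those are cases in which packing was performed, so they are successes by selection and say nothing about how often a flap cannot be raised.

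**Conclusion.** The concern holds as a risk created by the wording. The no-flap criterion can in practice be met only in Group A, and it stands beside withdrawal and loss to follow-up. The exclusion and complete-case rules then apply, with no as-randomised analysis to counter them.

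A reader might go further and conclude that the analysed groups will certainly differ from those randomised, that feasibility will be overstated, or that the non-inferiority result is at stake. The text does not establish the first two, since removal is inferred and a woman with full follow-up could be kept. The third is unlikely: across the assumed 5% to 20% removal, with fistula risk in the removed women from half the average to 30%, the upper limit stayed below 15 points even in the cell least favourable to Group A. The direction of bias cannot be settled from the documents. The rule should be corrected before analysis, but it does not by itself undermine the trial.

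**What to change.** - In {11b}, state that lack of a usable flap ends only the flap step. The woman stays in follow-up.
- In {11d}, {20a} and {20c}, state that every randomised patient with a fistula outcome is analysed in her allocated arm, whatever operation she received.
- Keep a per-protocol analysis alongside, and require both to support non-inferiority. Retaining flap failures in Group A draws the arms together, which on its own makes non-inferiority easier to show.
- Report the number of Group A women with no usable flap out of all randomised to Group A, using the discontinuation reasons already monitored under {18b}.

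**Cost.** These are wording changes and one extra count. No patients or visits are added, since Table 1 already schedules fistula assessment to 60 months. The article does not say whether any woman already discontinued among the 96 recruited has been followed, so recovery of such outcomes cannot be taken for granted. The statistical price is slight dilution of a true effect. If the flap halved the rate to 4.95% and an assumed 10% of Group A went without it, the as-randomised Group A rate would be 0.9 x 4.95 + 0.1 x 9.9 = 5.4%.

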#### Secondary outcomes

The occurrence time of postoperative RVF.The occurrence time of RVF after stoma closure.Postoperative complications, such as anastomotic leakage, chylous leakage, and intestinal obstruction.Postoperative serological test indexes, such as FSH, LH, E2, CEA, and CA199.Others about evaluating surgical methods, such as the duration of the operation, quality of life, abnormal discharge in the vagina.

The score of a functional assessment of cancer therapy (FACT) system will be used to evaluate the patient’s quality of life.

All data about the outcome will be collected according to the follow-up timepoint in Table 1. Measurement data between the two groups will be analyzed with the *t*-test and rank-sum test, while categorical data will be analyzed with *χ*^2^ test. The duration time will be recorded as mean ± standard deviation, and the incidence data will be recorded as median (first quartile, third quartile). The significance level used for statistical analysis will be two-sided with confidence intervals at the 95% level. All results will be applied to analyze the reliability of the new operation method, and to explore whether this new operation method will cause changes in the related complications, female hormones, affect the effect of the operation, and quality of life.

**Table 1 Tab1:** Schedule of enrolment, intervention, and assessments

Timepoint	Screening	Baseline	Intervention		Follow-up(months)											
			**Before**	**After**	**0**	**3**	**6**	**9**	**12**	**15**	**18**	**21**	**24**	**36**	**48**	**60**

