#### Samples

It is expected that the total number of samples would reach 80–100. The cases and controls were grouped according to the experimental protocol, and mid-term experimental data would be collected to analyze the expected risks of intervention measures. When adverse events or other related complications occur, patients who consider adverse outcomes would be reported by the research team and analyzed to determine whether their adverse events are related to the trial, and the research team would fulfill their obligation to inform and respect the patient's right to know related content. In the case of mid-term analysis, if there is no statistically significant difference between the case group and the control group or there are more adverse complications in the case group compared to the control group, the trial can be considered for discontinuation and protocol modification can be carried out. If there are significant modifications during the implementation process, the main researcher shall write and sign a “protocol modification manual” and submit it to the ethics committee for approval before implementation.

In the study, if the analysis results have no clinical significance due to the number of cases, the experimental time will be extended. The interim analysis report will be publicly released by the research participants.

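### A woman judged unable to continue because of a postoperative complication can leave the study, with no stated RVF follow-up afterwards and no place in the analysis

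*Protocol article*

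**What the plan says.** Section {11b} gives the criteria for discontinuing or modifying the allocated intervention. One item reads: "The patient would be unable to continue the protocol due to other postoperative complications". It stands next to a patient's request to withdraw and loss to follow-up.

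Under Secondary outcomes the article lists "Postoperative complications, such as anastomotic leakage, chylous leakage, and intestinal obstruction". Table 1 schedules these events, and the primary outcome RVF, at every visit from month 3 to month 60. The interim analysis section names "more adverse complications in the case group compared to the control group" as one ground for considering discontinuation of the trial.

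Section {11d} says that other complications of the procedure can be handled within the trial, and that further treatments and "concomitant medications will be determined by clinical need and will be recorded in follow-up case report forms". The same section says: "Patients who drop out of the experiment during the course of the study will be no longer included in the analyses". It adds: "Patients with other fatal complications will be no longer included in the analyses". Section {20a} says: "Patient data that falls off will not be included in the analysis". Section {20c} restricts the final analysis to cases with all required data complete.

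**The concern.** A postoperative complication happens after randomisation, and the added dissection of the flap may change how often it happens. If such an event can end a woman's participation, the women who remain are selected on an outcome. If those who leave have a higher RVF risk than those who stay, observed RVF falls in both arms, and falls further in the arm with more exits. That arm can then look better on the primary outcome because it had more complications.

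The complication comparison is exposed too, since women whose complication led to exit may be missing from the analysed set. The same applies at the interim look if the same exclusions are used there. RVF status that was never collected cannot be restored by a later choice of analysis, so this is more than a matter to leave to an analysis plan.

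**Working it through.** **What the item can mean.** By the Intervention description {11a}, the groups differ by one step within a single operation. After surgery no allocated intervention is left to stop or modify. What remains is Table 1 follow-up. With withdrawal and loss to follow-up in the same list, the item can only act as exit from the study.

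**Which events it covers.** The Methods part of the Abstract uses the same term, other postoperative complications, and gives anastomotic leakage, chylous leakage and obstruction as examples, labelled secondary outcomes. The exit item and the secondary outcome thus describe the same class of event. The item applies only to women judged unable to continue, and no criterion for that judgement is given. Section {17a} says patients and caregivers are not blinded, so the judgement could differ by arm.

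**What happens after exit.** Table 1 has no rule for women who exit. Section {18b} provides telephone, email or text contact but does not say that it continues after a {11b} exit. Sections {11d}, {20a} and {20c} exclude drop-outs and incomplete cases. A woman who leaves early after surgery has most of the RVF schedule still ahead of her.

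**Size for RVF (illustration).** The article gives no figure for this point to reproduce. From Sample size {14}: true RVF 9.9% in both arms. Assumed: exit share q and RVF risk r among those who exit. Observed RVF among those who remain is

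(0.099 − q × r) / (1 − q)

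| q | r = 0.20 | r = 0.30 |
|---|---|---|
| 0.10 | (0.099 − 0.020)/0.90 = 8.8% | (0.099 − 0.030)/0.90 = 7.7% |
| 0.15 | (0.099 − 0.030)/0.85 = 8.1% | (0.099 − 0.045)/0.85 = 6.4% |
| 0.20 | (0.099 − 0.040)/0.80 = 7.4% | (0.099 − 0.060)/0.80 = 4.9% |

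- Exits 20% v 10%: false difference 1.4 points (r = 0.20) to 2.8 points (r = 0.30).
- Exits 15% v 10%: 0.7 to 1.3 points.
- If r = 0.099, or if q and r are the same in both arms, the false difference is zero.
- The sign favours whichever arm has more exits.

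**Size for complications (illustration).** With true complication rate c and a share w of those women removed, the analysed rate is c(1 − w)/(1 − c × w). Assume c = 20% v 10% and w = 0.5. The analysed rates are 0.10/0.90 = 11.1% and 0.05/0.95 = 5.3%. A true gap of 10 points shrinks to 5.8.

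**The case against.** A reader might infer that outcome collection stops in every woman with a complication. The article does not say so. Section {11b} is headed as concerning the intervention and does not mention data collection. Table 1 contains no stopping rule, section {18b} provides remote contact, and its examples of study discontinuation are withdrawn consent and loss to follow-up. The item reaches only women unable to continue, and nothing says that a leak by itself makes a woman so. What stands is that no section keeps follow-up going once a woman has exited.

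A reader might also take {11d} as saying the opposite of {11b}. It does not: complications in general can be managed in the trial while the few women who cannot continue leave it. The two sections are in tension and leave the status of a particular woman open.

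Nor can it be said that the complication causing exit goes unrecorded. It has been observed by then, and section {22} has all adverse events recorded and reported to the ethics committee. It can be lost from the comparison only through the exclusion rules in {11d}, {20a} and {20c}.

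Finally, the size is assumed throughout. The article gives no complication rate, exit share or RVF risk after a complication. A 20% exit share for complications alone would use up the whole 20% loss allowance in section {14}. A bias of 0.7 to 2.8 points is small beside the stated 15% margin, and nothing shows that it would change the trial's conclusion. All of this is fair. But the stated objective is efficacy in preventing RVF, and against an assumed rate of 9.9% the same bias is 0.7/9.9 = 7% to 2.8/9.9 = 28% of the rate.

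**Conclusion.** The point holds in limited form. Read with the rest of the article, {11b} lets an event of the kind counted as a secondary outcome become a reason to leave the study. No provision is made for collecting RVF status afterwards, and other sections remove women who leave. Loss from the RVF and complication comparisons can therefore depend on outcome and may differ by arm.

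Its size cannot be established from the article. The range of 0.7 to 2.8 points rests on three assumptions: unequal exits (15 to 20% v 10%), an RVF risk of 20 to 30% in those who exit, and the article's 9.9% in both arms. It could favour either group, and it vanishes if exit is unrelated to RVF risk. The defect lies in the rule itself and does not depend on that illustration.

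**What to change.** Either remove the postoperative-complication item from {11b} as a reason to leave the study, or state that it ends protocol procedures only. Reconcile it with {11d}. Then add wording such as:

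*After surgery, no complication ends follow-up. The RVF and complication assessments in Table 1 continue until month 60, death, or withdrawal of consent for follow-up. If a patient cannot attend, RVF and complication status are obtained by telephone or from hospital records. These patients remain in the analysis.*

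The exclusion sentences in {11d} and {20a} and the complete-case rule in {20c} need matching changes, or the last sentence of the addition will have no effect. Clinical care of complications is not touched.

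The cost is a protocol amendment. Section {25} requires resubmission to the registry and ethics re-approval, and re-consent where the change differs from what participants were told. There is some extra follow-up contact, for which {18b} already names the means. Trial status reports 96 women recruited with recruitment still open, so much of the follow-up to month 60 can still be protected. Follow-up already missed may not be recoverable; any exits so far under this item should be counted and reported by arm.
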